# INFERR-Iron infusion in haemodialysis study: INtravenous iron polymaltose for First Nations Australian patients with high FERRitin levels on haemodialysis—a protocol for a prospective open-label blinded endpoint randomised controlled trial

**DOI:** 10.1186/s13063-021-05854-w

**Published:** 2021-12-02

**Keywords:** Aboriginal and Torres Strait Islander Australians, First Nations Australians, Anaemia, Chronic kidney disease, Maintenance haemodialysis, Ferritin, Iron deficiency, Intravenous iron

## Abstract

**Background:**

The effectiveness of erythropoiesis-stimulating agents, which are the main stay of managing anaemia of chronic kidney disease (CKD), is largely dependent on adequate body iron stores. The iron stores are determined by the levels of serum ferritin concentration and transferrin saturation. These two surrogate markers of iron stores are used to guide iron replacement therapy. Most Aboriginal and/or Torres Islander Australians of the Northern Territory (herein respectfully referred to as First Nations Australians) with end-stage kidney disease have ferritin levels higher than current guideline recommendations for iron therapy. There is no clear evidence to guide safe and effective treatment with iron in these patients. We aim to assess the impact of intravenous iron treatment on all-cause death and hospitalisation with a principal diagnosis of all-cause infection in First Nations patients on haemodialysis with anaemia, high ferritin levels and low transferrin saturation

**Methods:**

In a prospective open-label blinded endpoint randomised controlled trial, a total of 576 participants on maintenance haemodialysis with high ferritin (> 700 μg/L and ≤ 2000 μg/L) and low transferrin saturation (< 40%) from all the 7 renal units across the Northern Territory of Australia will be randomised 1:1 to receive intravenous iron polymaltose 400 mg once monthly (200 mg during 2 consecutive haemodialysis sessions) (Arm A) or no IV iron treatment (standard treatment) (Arm B). Rescue therapy will be administered when the ferritin levels fall below 700 μg/L or when clinically indicated. The primary outcome will be the differences between the two study arms in the risk of hospitalisation with all-cause infection or death. An economic analysis and several secondary and tertiary outcomes analyses will also be performed.

**Discussion:**

The INFERR clinical trial will address significant uncertainty on the safety and efficacy of iron therapy in First Nations Australians with CKD with hyperferritinaemia and evidence of iron deficiency. This will hopefully lead to the development of evidence-based guidelines. It will also provide the opportunity to explore the causes of hyperferritinaemia in First Nations Australians from the Northern Territory.

**Trial registration:**

This trial is registered with The Australian New Zealand Clinical Trials Registry (ANZCTR): ACTRN12620000705987. Registered 29 June 2020.

**Supplementary Information:**

The online version contains supplementary material available at 10.1186/s13063-021-05854-w.

## Administrative information

Note: the numbers in curly brackets in this protocol refer to SPIRIT checklist item numbers. The order of the items has been modified to group similar items (see http://www.equator-network.org/reporting-guidelines/spirit-2013-statement-defining-standard-protocol-items-for-clinical-trials/).

**Table Taba:** 

Title	INFERR-Iron Infusion in Haemodialysis Study: INtravenous Iron Polymaltose for First Nations Australian Patients with High FERRitin Levels on Haemodialysis: A Protocol for a Prospective Open-Label Blinded Endpoint Randomised Controlled Trial
Trial registration {2a and 2b}.	Trial registry name: The Australian New Zealand Clinical Trials Registry (ANZCTR) Trial identifier: ACTRN12620000705987
Protocol version {3}	27th August 2020; Version 2.0,
Funding {4}	The trial is funded by National Health and Medical Research Council (NHMRC) Project Grant #1163841

## Introduction

### Background and Rationale{6a}

Rates of dialysis-requiring end-stage kidney disease (ESKD) among Aboriginal and Torres Strait Islander Australians (herein respectfully referred to as First Nations Australians) of the Northern Territory (NT) are some of the highest in the world [1, 2]. Anaemia is a major complication of ESKD [3]. Prevalence rates of anaemia are also high among First Nations Australians [4–6]. Anaemia is associated with reduced quality of life, increased risk of cardiovascular disease, hospitalisations, cognitive impairment, and mortality [7, 8]. Therapy with erythropoiesis-stimulating agents (ESAs) is the main approach for correcting anaemia in people with chronic kidney disease (CKD) and work most effectively when the patient is replete in iron stores. The appropriate use of ESAs improves quality of life and reduces morbidity and mortality [3]. One of the major causes of anaemia in people with CKD is iron deficiency [9]. Iron deficiency is also the commonest cause of poor response to ESA therapy [10, 11].

The effective treatment of anaemia in maintenance haemodialysis (MHD) patients therefore requires both the accurate assessment of iron status, and the safe and appropriate correction of iron deficiency. Several published guidelines are available to guide iron replacement in patients with CKD [12–15] (Supplementary Table 1). Iron therapy using these guidelines is largely dependent on the levels of serum ferritin and transferrin saturation (TSAT) [the ratio of serum iron to the total iron-binding capacity (TIBC) as a percentage], both surrogate markers of iron status. Ferritin is an intracellular protein which stores excess iron, and low serum ferritin is a marker of iron deficiency. However, ferritin is also an acute phase protein, and increased serum ferritin concentration, along with increases in other acute phase reactants such as C-reactive protein (CRP), is observed in patients who have inflammation [6, 16]. There is also growing evidence that high serum ferritin concentration is independently associated with high rates of hospitalisations, cardiovascular disease and mortality [6, 17, 18].

True iron deficiency is indicated by the co-occurrence of both low ferritin and low TSAT levels. Functional iron deficiency is characterised by an impaired iron release from body stores [19]. This is thought to be due to reticuloendothelial cell iron blockade; serum ferritin is normal or high and serum TSAT levels are low. In patients with CKD, both true iron deficiency and functional iron deficiency need treatment with iron replacement therapy [14]. In First Nations Australians in the NT, anaemia in MHD patients co-exists with ESA-hyporesponsiveness, high serum ferritin concentrations and high serum CRP [16] in a population with heavy burden of cardiovascular, infectious diseases, hospitalisations and premature mortality. High serum ferritin levels have been recognised in this population for almost 20 years, and since these levels may be due to chronic inflammation [16, 20–23], there is significant uncertainty regarding the appropriate management of anaemia [16, 23] using serum ferritin levels as a marker of iron status. The recently replaced NT iron management protocol was developed to guide iron replacement in MHD patients with serum ferritin levels above 500μg/L associated with low TSAT (Supplementary Table 2). Evidence to guide safe and effective use of intravenous iron in this population is urgently required.

In a study of the effectiveness of this protocol in correcting iron deficiency in 197 NT patients on MHD, we found patients were poorly responsive to ESA treatment and received higher annual doses of iron treatment both in absolute terms and relative to the haemoglobin response [16]. In another cohort, high ferritin levels in First Nations MHD patients were only partly explained by iron sufficiency as indicated by high TSAT [23]. The retrospective design of these 2 studies meant that the possible presence of iron overload [24], which is a clear risk in this situation, could not be determined. Despite this, the higher iron doses observed [16] suggest iron overload is a potential harm. We thus identified the need for a prospective study to investigate the safe and effective administration of iron among First Nations patients on MHD with high ferritin levels [16, 23, 24].

Findings of studies that we conducted in the NT [6, 16, 23] and evidence from other international studies demonstrate a need to use serum ferritin levels and TSAT in conjunction with other markers of iron status, particularly in patients with a high serum ferritin concentration. A report from the United Kingdom National Institute for Health and Care Excellence (NICE) has discouraged the use of either measure alone due to significant problems with lack of accuracy in determining the correct treatment [14]. Other potential markers of iron status include hepcidin [25–27], soluble transferrin receptor [28] (shown to be a better marker of iron stores than ferritin in First Nations children) [29], low mean corpuscle volume (MCV) and hypochromic, microcytic RBCs on blood film, percentage hypochromic red cells (PHRC) and reticulocyte haemoglobin content [30].

One potential and unexplored cause of high ferritin is the association with the metabolic syndrome in our patients [31]. Metabolic syndrome and diabetes are highly prevalent conditions among First Nations ESKD patients, but the association with raised ferritin has not been investigated. Examining the association of ferritin with more specific inflammatory markers such as interleukin-6 (IL-6) and tumour necrosis factor-α (TNF-α) will help to confirm if the ferritin is due to causes other than inflammation [32, 33].

A recent study showed that serum ferritin (200–500 μg/L) correctly reflected liver iron stores, as assessed by magnetic resonance imaging (MRI) (FerriScan®), in haemodialysis patients without overt inflammation or malnutrition [34]. The authors concluded that current ferritin target values should be lowered to avoid iron overload. However, ferritin levels in their patients were much lower than in our First Nations MHD patients [34]. Another study has the opposite conclusion that transferrin saturation and serum ferritin levels were poor markers of liver and cardiac iron deposition in MHD subjects [35]. In patients with high ferritin levels receiving iron treatment, it is crucial to monitor iron overload by measuring liver iron non-invasively with MRI-FerriScan® [36, 37]. Monitoring liver fibrosis (using FibroScan®) and cirrhosis is also crucial [31, 38–40]. Considering the high prevalence of diabetes mellitus and metabolic syndrome in the First Nations Australian population, it may be hypothesised that a high prevalence of hepatic steatosis and fibrosis exists as encountered in dialysis patients more and more frequently in developed countries as well as the dysmetabolic iron overload [6]. There is a need to identify those patients with these underlying liver diseases, to adapt iron dosage and to monitor the safety of IV iron in this setting. This peculiar safety issue seems particularly relevant since indiscriminate IV iron has recently been shown to either trigger or aggravate non-alcoholic fatty liver disease / non-alcoholic steatohepatitis in dialysis patients suggesting a double-edged iron sword [6].

In some studies, iron treatment has been associated with adverse effects (infections, cardiovascular complications and hospitalisations) especially if doses of > 1000 mg are given over 6 months [41]. Our patients are already at high risk of infections such as high rates of melioidosis during the wet season and high prevalence cardiovascular disease [42, 43].

Current evidence of treatment in patients with high serum ferritin levels is from two North America clinical trials. The Dialysis Patients’ Response to IV Iron with Elevated Ferritin (DRIVE) study showed that administration of ferric gluconate (125 mg for eight treatments) was superior to no iron therapy in anaemic dialysis patients receiving adequate ESA dosages with a ferritin 500 to 1200 ng/ml and TSAT ≤ 25% [44]. In our patient population, only 5.6% of the First Nations patients would fit entry criteria for the DRIVE study [16].

The follow-up DRIVE II study was a 6-week observational extension of DRIVE which concluded that ferric gluconate maintained haemoglobin and allowed lower ESA doses [45]. These two studies partly informed the development of our recently replaced treatment protocol tailored to the high levels of ferritin in our patients (supplementary Table 1).

In The Proactive IV irOn Therapy in hemodiALysis patients (PIVOTAL) trial, incident (< 12 months) haemodialysis patients were randomised 1:1 to high-dose IV iron sucrose versus a reactive low-dose IV iron sucrose in haemodialysis patients across the UK [46–48]. Patients with ferritin levels > 700 μg/L were excluded. The trial confirmed the safety and efficacy of high-dose IV iron at a maximum dose of 400 mg of iron once a month [46].. The exclusion of patients with high ferritin makes the results of this trial not generalisable to our First Nations dialysis population since over 80% of the patients have a ferritin higher than 700 μg/L [16].

In a new protocol used by dialysis units across the NT for patients with ferritin < 700 μg/L and TSAT < 40%, a maximum dose of 400 mg of IV iron once monthly is convenient and provide the best current evidence based on the PIVOTAL trial for dosing IV iron in dialysis patients (see additional file 1).

The INFERR clinical trial assesses the efficacy of IV iron in First Nations MHD patients with high serum ferritin levels. We hypothesise that intravenous iron therapy will safely and effectively improve haemoglobin concentration and reduce the frequency of anaemia among First Nations Australians on MHD who have anaemia with low transferrin saturation (less than 40%) coexisting with high serum ferritin concentrations (> 700 μg/L and less ≤ 2000 μg/L).

### Objectives {7}

#### Primary objective

The primary objective is to assess the impact of intravenous iron treatment on all-cause death and hospitalisation with a principal diagnosis of all-cause infection in First Nations patients on MHD with anaemia, high ferritin levels and low transferrin saturation

#### Secondary objectives

The secondary objectives are as follows: (1) to document serious adverse events – major cardiovascular events, rates of infections and all-cause hospitalisation rates associated with the intravenous iron therapy [2]. To assess the relationship between ferritin, total body iron levels, measures of iron status, inflammation and liver disease [3]. To determine the costs that associate with intravenous iron treatment in this setting.

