#### Major events

Hospitalisation due to all-cause infections or death are documented as the primary outcome. All admissions overnight or longer are followed up with collection of detailed data on the admission. Data on all major vascular events, all dialysis access-related events including infections and vascular interventions not requiring hospital admission are also collected.

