### Composition of the data monitoring committee, its role and reporting structure {21a}

#### Data safety and monitoring board (DSMB)

An independent DSMB (none of whom are chief investigators or associate investigators) has been established to review the progress of the study and monitor adherence to the protocol, participant recruitment, outcomes, complications and other issues related to participant safety. They also monitor the assumptions underlying sample size calculations for the study and alert the investigators if they see substantial departures from the assumptions as the data accumulate.

The DSMB includes two clinician-researchers familiar with clinical trials, a statistician, and a First Nations clinical researcher. The DSMB met before recruitment commenced and 6 months following commencement of recruitment and will continue to meet at annual intervals and at its conclusion. Progress reports documenting serious adverse events will be provided to the DSMB 6-monthly. We have planned a formal interim analysis.

The DSMB will make recommendations as to whether the study should continue or be terminated and consider participant safety or other circumstances as grounds for early termination, including either compelling internal or external evidence of treatment differences or feasibility of addressing the study hypotheses (e.g. poor participant enrolment, poor adherence).

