### Adverse events reporting and harms {22}

#### Serious adverse events (SAEs)

A SAE is defined as any experience that:
Results in deathIs life threatening.
The term “life threatening” refers to an event in which the participant was at risk of death at the time of the event. It does not refer to an event which hypothetically may have caused death if it were more serious.Results in unexpected prolongation of existing hospitalisationResults in persistent or significant disability/incapacityIs a medically important event or reaction.

All SAEs that are considered related to the study drugs require reporting on the SAE form. If the SAE is attributable to disease progression, then this does not require expedited reporting in this trial, even when death is the outcome. The site PI is required to report any SAEs that occur at their site to the approving ethics committee in accordance with local guidelines; in addition, the site PI must adhere to any local institutional reporting requirements and study sponsor. Safety reporting will be in line with the National Health and Medical Research Council’s (NHMRC) Guidance: Safety monitoring and reporting in clinical trials involving therapeutic goods (2016) [53].

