#### Suspected unexpected serious adverse reactions (SUSAR)

An adverse event that is both serious and unexpected (not listed in the product information and not attributable to disease progression) and related to the study drug meets the definition of a SUSAR. All SUSARs must be entered on the SAE CRF and reported to the sponsor or delegate within 24 h from the time of the site study team becoming aware of it. If the SUSAR is fatal or life threatening, the Sponsor will report to the TGA within 7 calendar days of becoming aware and any follow-up reports required within a further 8 calendar days, and for all others 15 calendar days of becoming aware.

The site PI is required to report any SUSARs that occur at their site to the approving ethics committee in accordance with local guidelines; in addition, the site PI must adhere to any local institutional reporting requirements. Safety reporting will be in line with the NHMRC’s Guidance: Safety monitoring and reporting in clinical trials involving therapeutic goods (2016) [53].

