##### Summary of expedited reporting of adverse events and adverse drug reactions

In summary, SAEs *not* thought to be related to the study drug do not need to be reported in this trial; however, this data will be collected for outcome measures. SAEs thought to be possibly, probably or definitely related to study drug (e.g. an anaphylactic reaction to IV iron) must be reported by the PI or CI, research nurse or their delegate to the sponsor (in this case the Clinical Trial Manager and CIs at Menzies) within 24 h of becoming aware of the event. Reporting to the HREC will be in accordance with local guidelines. If it is an expected side effect (i.e. one listed in the product information, such as allergic reaction or diarrhoea), it does not need to be reported to the TGA. If it is both *unexpected* and serious, it needs to be reported to the TGA within 7 days (fatal or life threatening) or 15 days (other).

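### The secondary safety objective and outcome list treat hospital admissions as serious adverse events, but the SAE definition covers only prolongation of an existing stay, not a new admission

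*Protocol article*

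**What the plan says.** Under Secondary objectives, the protocol article sets out "to document serious adverse events – major cardiovascular events, rates of infections and all-cause hospitalisation rates". The dash presents cardiovascular events, infections and hospitalisations as the content of the term SAE.

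Secondary outcomes {12} has an SAE item followed by four entries: all SAEs, all admissions to hospital, infections linked to hospitalisation, and mortality from any cause.

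The section Serious adverse events (SAEs), under Adverse events reporting and harms {22}, gives the definition in five criteria. They are death, threat to life, unexpected lengthening of a stay already under way, persistent or significant disability, and medical importance. The second is narrowed by the explanation that it "refers to an event in which the participant was at risk of death at the time of the event". Starting a hospital stay is not a criterion.

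Three further uses rest on the definition:

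- Data safety and monitoring board (DSMB): "Progress reports documenting serious adverse events will be provided to the DSMB 6-monthly".
- The summary of expedited reporting requires SAEs possibly, probably or definitely related to the study drug to reach the sponsor within 24 hours.
- The SUSAR section begins with "An adverse event that is both serious and unexpected" and adds relatedness to the study drug.

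Admissions are also recorded independently of SAE status. Under Major events, "All admissions overnight or longer are followed up with collection of detailed data on the admission".

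**The concern.** The objective and the outcome list use one meaning of SAE and the harms section defines another. Under the definition, lengthening a stay is serious by rule, while causing one is not.

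A non-fatal admission that is not life threatening, not disabling and not a prolonged stay can then become an SAE only through the medical-importance criterion, which is a judgement. Who is blinded {17a} states that investigators know the allocation. In an open-label comparison of iron with no iron, that puts an arm-aware decision between the event and a safety outcome compared by arm.

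Seriousness is also settled before relatedness. This is therefore a separate matter from the protocol's choice to expedite related SAEs only: an event not classed as serious never reaches the question of relatedness on that route. The protocol's own background names infections and hospitalisations among the adverse effects associated with iron treatment in some studies, so these are the admissions for which a clear rule matters.

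**Working it through.** No arithmetic applies. The check is whether an ordinary admission is an SAE under each part of the text. Take a participant admitted for several nights with an infection who recovers, was never at risk of death and has no lasting disability.

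| Place in the protocol article | Is this admission an SAE? |
|---|---|
| Secondary objectives | Yes. Infections and all-cause hospitalisation are named as what the SAEs are. |
| Secondary outcomes, SAE item | Yes, if the four entries are read as sub-items. |
| Definition: death | No. |
| Definition: life threatening | No. Actual risk of death at the time is required. |
| Definition: prolongation | No. There was no existing stay to prolong. |
| Definition: disability | No. |
| Definition: medically important | Only if someone judges it so. |

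The same holds for a heart failure or myocardial infarction admission that was not life threatening.

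Consequences, taken in turn:

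1. **All-SAE comparison by arm.** If the definition is applied, this total can be smaller than the admissions listed under the same item. If the objective is applied, it cannot. The two readings give different totals from the same data.
2. **DSMB reports.** The SAE part of the 6-monthly report inherits whichever reading is used.
3. **24-hour report and SUSAR route.** Both require the event to be serious. A related admission not judged medically important would enter neither.
4. **Who judges.** The protocol assigns causality to the principal investigator or a delegate. It names nobody for seriousness and, in the section on the blinded adjudication committee, charges that committee with deciding whether the composite primary endpoint was met.

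No other section supplies a new-hospitalisation criterion. The definition shows no gap or redaction mark, and the data-access section {31c} states that the article gives the full study protocol, so neither text extraction nor condensation explains the omission.

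**The case against.** The strongest reply is that little depends on the label, and much of it stands.

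- **A reader might infer that admissions go uncounted or that the primary endpoint is damaged.** The documents do not support this. Overnight admissions are followed up in detail, and hospitalisations are collected at every 3-monthly visit. All-cause and infection hospitalisation, myocardial infarction, stroke and heart failure hospitalisation are time-to-first-event outcomes in their own right. For SAEs thought unrelated, the protocol adds: "however, this data will be collected for outcome measures".
- **A reader might infer that the DSMB does not see infection admissions.** It does. The unblinding section {17b} has it review primary endpoint events as well as SAEs, with descriptive analyses by arm label, and the interim analysis uses the primary outcome.
- **A reader might infer that a drug-caused admission escapes reporting altogether.** That also goes too far. The post-trial care section {30} sends all types of adverse event to the sponsor as soon as possible. The adverse drug reaction section collects suspected reactions within 24 hours of infusion whatever their seriousness, and summaries of reactions go to the DSMB and the ethics committee. These are partial backstops: the first sets no fixed deadline, the second would not cover an infection arising later, and none replaces the 24-hour SAE report or the SUSAR route.
- **The medical-importance criterion may catch many of these admissions.** It may. The point is only that an admission need not be an SAE under the definition, whereas the objective treats it as one.
- **The outcome list is run together in the article, so its nesting is partly inferred.** This is fair, but the wording of the objective carries the contradiction without it.
- **Independent assessors determine outcomes from the records.** They would be applying the same list with the same discretionary criterion, and expedited reports come from the research and site staff.
- **National guidance is cited and the SAE form is not shown.** The guidance is cited for safety reporting and its content is not available here. Practice at the sites may be better than the text, so confidence extends to the wording and not to trial conduct.

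**Conclusion.** The inconsistency stands. The objective and outcome list count hospital admissions as serious adverse events, and the definition does not. Three things are affected: the all-SAE comparison by arm, the SAE part of the 6-monthly DSMB reports, and the certainty that a drug-related admission enters the 24-hour and SUSAR routes. For these, a non-fatal, non-life-threatening admission depends on an arm-aware judgement of medical importance.

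No number of affected events can be derived. The 60% two-year rate in the sample size section does not separate infection admissions from deaths, and nothing shows what share of admissions would be life threatening or judged medically important. Any such count would in any case consist largely of events already captured as outcomes.

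The conclusion assumes that the printed definition is the one in use. It is worth correcting because safety reporting depends on it and the correction is cheap. It does not threaten the trial's main result.

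**What to change.** Reconcile the Secondary objectives, the SAE item in Secondary outcomes and the SAE definition:

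1. Add inpatient hospitalisation, overnight or longer, to the SAE criteria beside prolongation of an existing stay. This is the threshold already used for data collection under Major events. Exempt planned admissions if wanted, and say so.
2. Have the objective and the SAE outcome refer to that definition, and state whether the admissions entry includes same-day stays, so that the two lines can be compared.
3. Tabulate SAEs by arm and report them to the DSMB on the same definition, including events since recruitment began on 16 December 2020. Overnight admissions from that date can be recoded from data already collected.

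The cost is one line in the protocol and the SAE form, notification of the ethics committees as for any amendment, and more events coded as SAEs. Expedited reporting stays limited to related events, so the added urgent workload is confined to related admissions that would not otherwise have been judged serious.
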